### 2.7. Secondary Outcome Measures

 Change of tinnitus severity according to the tinnitus questionnaire of Tinnitus Handicap Inventory (THI) [26]:
(1.1) F: functional subscale (11 factors),(1.2)E: emotional subscale (9 factors),(1.3)C: catastrophic subscale (5 factors). 
Each question of the THI can be answered by the patient with either often (4 points), sometimes (2 point), or never (0 points) with a maximum total score of 100 indicating most severe suffering from tinnitus. The assessment is at baseline (before treatment initiation) and 3 weeks later of the first acupuncture. Participants also report adverse events induced by the acupuncture treatment, including discomfort or bruising at the sites of needle insertion, nausea, or feeling faint after each treatment. Answers concerning possible side effects related to the acupuncture treatment will be documented by using a standardised questionnaire at the end of treatment. 

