### 2.1. Recruitment

Patients will be recruited in acupuncture clinic, Beijing Hospital of Traditional Chinese Medicine affiliated to Capital Medical University with a target sample size of 30 subjects. The trial is executed from March 2012 to June 2013.

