### 2.5. Interventions

This trial is a randomized controlled study. Participants will receive acupuncture for 3 weeks (Figure 1) (twice per week). All candidates go through a standardized interview and receive more information about the study and the treatments. They also undergo audiological testing of hearing thresholds, minimal masking levels, and loudness discomfort levels carried out by an audiologist in Tongren Hospital affiliated to Capital Medical University ([name]).

Timepoints are as follow: visit 1: screening, visit 2: treatment initiation, participants will receive acupuncture for 3 weeks, visit 3: 3 weeks later of first acupuncture, followup and treatment finish.

Patients who meet the inclusion criteria and none of the exclusion criteria are randomized to one of two treatment groups. Group A will receive verum acupuncture (creating deqi sensation). Group B will receive shallow acupuncture (not creating deqi sensation).

Acupuncture points are selected as follow (Figure 2).

Patients are stimulated by 5 main acupoints: Baihui (Du-20), Shenting (Du-24), Tinghui (GB-2), Waiguan (SJ-5), and Zulinqi (GB-41). The acupoints are stimulated continuously by the true needles or the shallows for 20 minutes per session. 

Acupuncture is performed with sterile needles by one therapist ([name]) with more than 22 years of experience and an acupuncture license from the Chinese medicine practitioner from the Ministry of Health of China. Treatment will be conducted over a period of 3 weeks, at a frequency of 2 sessions/week. No additional treatment is allowed.

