## 3. Discussion

This trial has been designed above to identify whether acupuncture could (verum acupuncture or shallow acupuncture) treat subjective tinnitus patients by modulating HRV, so as to explain the mechanism of acupuncture effects on tinnitus. If this questionnaire results provide evidence for the safety of acupuncture, more patients with these conditions may be encouraged to seek out acupuncture. 

The present study aimed to help to draw more attention in acupuncture's potential for treating patients with tinnitus by autonomic regulation. Although a climate where acupuncture might be assumed to be ineffective exists [27, 28], there is inadequate evidence on which to base a judgment on acupuncture's effectiveness for tinnitus. Well-designed randomized controlled trials which can provide the acupuncture effect mechanism for tinnitus by scientific approach are needed.

Verum acupuncture is administered by twirling and lifting the needles until deqi occurred. One of the greatest challenges in acupuncture research is selecting an appropriate sham acupuncture control. There are several existing sham acupuncture methods including shallow needling on acupoint, shallow needling on nonacupoint and ritualized mock acupuncture. To avoide the difference of acupoint selection, shallow needling on acupoint is used as a control group in this trials. For the shallow group, the point selection is the same as the verum acupuncture group. However, the depth of needles inserted vertically to the subcutaneous level should be rigidly controlled over no more than 3 mm. Any sensation (deqi) or needle manipulation is prohibited in this group. Because the needles are inserted at the same points, the patients cannot distinguish the shallow acupuncture from the real one on the vision. 

Placebo effects of acupuncture are actively studied in many articles, and sham acupuncture is a representative method for an acupuncture placebo tool [29, 30]. But there is a lack of consensus on the most valid approach to establishing placebo acupuncture. Therefore, important aspects of the placebo acupuncture control need to be considered. In this trial, we will evaluate the effect of deqi on HRV and reveal the potential mechanism of acupuncture treatment for tinnitus.

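### The only named adverse event record is an end-of-treatment questionnaire, and the text does not say whether events are written down session by session

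*Protocol article*

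**What the plan says.** Safety is covered in two consecutive sentences at the end of section 2.7 of the protocol article. The first begins "Participants also report adverse events induced by the acupuncture treatment" and lists the events, "including discomfort or bruising at the sites of needle insertion, nausea, or feeling faint after each treatment". The second fixes the record: "Answers concerning possible side effects related to the acupuncture treatment will be documented by using a standardised questionnaire at the end of treatment". No other safety form or recording time is named.

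Section 2.5 sets the schedule: "Treatment will be conducted over a period of 3 weeks, at a frequency of 2 sessions/week". It dates the last visit as "visit 3: 3 weeks later of first acupuncture, followup and treatment finish". Section 2.1 gives the size of the trial, "with a target sample size of 30 subjects".

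The Discussion (section 3) then says: "If this questionnaire results provide evidence for the safety of acupuncture, more patients with these conditions may be encouraged to seek out acupuncture".

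**The concern.** The listed events are mostly minor and brief, and each of six sessions can produce them. A single form at the end of the course is a poor instrument for such events. A patient who completes the course must recall slight complaints from weeks before, and a patient who stops after an early session may never reach the form. Both mechanisms would lower the count.

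The Discussion raises the stakes. It treats the questionnaire as possible evidence of safety that could lead more patients to seek the treatment. A low count produced partly by the timing of the form would look the same as a low count produced by safe needling.

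**Working it through.** The article states no safety figure to reproduce. The check compares the readings of the text, then works out the recall interval and the precision available.

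**1. What the two sentences can mean.** Two phrases in section 2.7 are open: the timing words that close the list of events, and the end of treatment.

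| Timing words attach to | End of treatment means | Consequence |
|---|---|---|
| feeling faint only | end of the course | one written record, at the end |
| the act of reporting | end of the course | events are voiced after each session, but the only named record is at the end; whether the reports are written down at the time is not stated |
| either | end of each session | recorded session by session; little recall problem |

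For the second phrase, the end of the course is the more natural reading. Section 2.5 puts the finish of treatment at visit 3, and section 2.7 uses the initiation of treatment for the start of the course. But section 2.7 also uses the word treatment for a single session, so the text does not settle it.

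**2. Number of sessions** (section 2.5): 3 weeks × 2 per week = 6.

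**3. Recall interval if the end form is the only record.** Even spacing is an assumption: 7 / 2 = 3.5 days. Session k then falls on day 3.5 × (k − 1), so session 6 falls on day 3.5 × 5 = 17.5. Visit 3 falls on day 21.

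| Session | Day | Recall, form at session 6 (days) | Recall, form at visit 3 (days) |
|---|---|---|---|
| 1 | 0 | 17.5 | 21 |
| 2 | 3.5 | 14 | 17.5 |
| 3 | 7 | 10.5 | 14 |
| 4 | 10.5 | 7 | 10.5 |
| 5 | 14 | 3.5 | 7 |
| 6 | 17.5 | 0 | 3.5 |

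With a form at each session that covers the time since the last one, the interval falls to about 3.5 days.

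**4. What a zero count could show, with perfect capture.** The exact one-sided 95% upper limit for zero events in n patients solves (1 − p)^n = 0.05, so p = 1 − 0.05^(1/n).

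- All patients, n = 30 (section 2.1): 1 − 0.05^(1/30) = 0.095, or 9.5%.
- One arm, n = 15 (assuming equal arms): 1 − 0.05^(1/15) = 0.181, or 18.1%.

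These limits reflect the size of the trial and not the timing of the form. They show how far the statement in the Discussion could go at best. Incomplete capture weakens it further, by an amount the document gives no means to estimate.

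**The case against.** The strongest reply is that the sentence before the one on documentation may already provide for reporting after every session. On that reading recall is at most a few days. This is a fair reading, and it rules out saying flatly that adverse events are collected only once. It does not remove the point, because the sentence that fixes the documentation still names only the end of treatment and the two are not joined up.

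A reader might also infer that patients who stop early go unrecorded. The article does not say so. It is silent on adverse event recording at discontinuation, which a condensed article may leave to the full protocol, and it says the trial follows Good Clinical Practice. What stands is narrower: the timing that is stated gives such a patient no capture point.

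A reader might further infer that the loss would differ between arms, because only the verum needles are manipulated until deqi. That is possible, but nothing in the document shows it or allows it to be sized.

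Finally, the safety sentence in the Discussion is conditional, not a planned conclusion, and it does not name the questionnaire. The Tinnitus Handicap Inventory is called a questionnaire too, but it measures tinnitus handicap and says nothing about needling safety, so the side-effect form is the sensible referent. The article already acknowledges the limited sample size, and the primary outcome, heart rate variability, is unaffected.

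**Conclusion.** The point holds as an ambiguity with a likely direction of error and a cheap remedy. It does not show that events will be lost. If the end-of-treatment form is the only written record, and sessions are evenly spaced, first-session events rest on 17.5 to 21 days of recall, early stoppers have no stated capture point, and counts are likely to be too low. The size of the shortfall cannot be derived from the document.

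If reports are in fact written down after each session, the recall problem largely disappears and only the wording needs repair. Under either reading, a clean record supports no more than an upper limit of 9.5% in 30 patients, or 18.1% in an arm of 15, so the Discussion should not treat it as evidence of safety without those limits. The stronger statements, that early stoppers go unrecorded or that one arm loses more events than the other, are possibilities only.

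**What to change.** Reconcile the two sentences in section 2.7. State that the existing standardised questionnaire is completed at each of the six sessions, covering events since the previous one, again at visit 3 for the time after the last session, and at discontinuation for anyone who stops. Report events by arm for every patient who was needled. In the Discussion, name the questionnaire that is meant, and limit the safety statement to observed rates with exact confidence limits.

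Patients already attend these sessions and the form exists, so the cost is a few minutes per session. Minor events will probably be reported more often than with one form at the end. The change concerns data collection and reporting only.

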### 2.8. Data Analysis

We use paired *t*-tests and two-way ANOVA with one repeated measure to analysis the data of 30 tinnitus patients. Post hoc analyze is performed using Tukey test. The level of significance is defined as *P* < 0.05. 

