## Abstract

*Background*. Recent reports suggest that a proportion of tinnitus patients suffer from mental illness. Autonomic nervous system plays a useful role in tinnitus therapy since electrical vagal nerve stimulation (VNS) has been frequently used to alleviate tinnitus-induced depression in clinic. heart rate variability (HRV), which is reflective of autonomic nervous system function, has been proved to be modulated by acupuncture. In the present study, we aim to compare the effect of deqi sensation on heart rate variability in adult tinnitus patients. *Methods*. Thirty participants are randomly assigned to verum acupuncture (creating deqi) or shallow acupuncture (not creating deqi) at Baihui (Du-20), Shenting (Du-24), Tinghui (GB-2), Waiguan (SJ-5), and Zulinqi (GB-41) for 3 weeks. The primary outcome measure is heart rate variability, which is measured at the first acupuncture, as well as the last acupuncture. *Discussion*. Completion of this trial will help to identify the role of deqi sensation in acupuncture effect for tinnitus and reveal an autonomic modulation mechanism for acupuncture effect. *Trial Registration*. This trial is registered with International Standard Randomised Controlled Trial Number ISRCTN58013563.

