### 2.4. Randomisation and Blinding

After participants complete a baseline evaluation, a research coordinator ([name]) who is uninvolved with data collection randomly allocates them to either verum acupuncture group or shallow acupuncture group by using a computer-generated, blocked random-allocation sequence with a block size of 6. The random codes are only known by another researcher ([name]) who is not involved in treatment and statistical analysis.

The assignment is done in a single-blind manner, in which the patients are blinded to treatment assignment. In order to minimize the placebo effects, patients are informed in a manner suggesting that two different types of acupuncture treatment are compared. One type is traditional acupuncture, another is novel acupuncture, and the effect of both is uncertain. Similar strategies of informed consent have been used in most previous acupuncture trials [24]. HRV analysis and assessment of THI are performed by a researcher ([name]), who is blinded to patients' treatment respectively. During the intervention, acupuncturist and all the researcher personnel are segregated immediately after the treatment starts and are instructed not to exchange information with each other.

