### 2.6. Primary Outcome Measures

HRV indexes are measured using a digital 12 leads ECG-Holter machine (Mortara Instruments, USA). Within frequency domain, power in low frequencies (LF; 0.04–0.15 Hz), and in high frequencies (HF; 0.15–0.4 Hz) are calculated for each 5-minute density spectrum by integrating the power spectral density in the respective frequency bands. The HF/LF ratio also is analyzed [25]. HRV is measured at the first acupuncture, as well as the last acupuncture (Figure 3).

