**Figure 3 fig3:**
[figure not shown]
Sequence for heart rate variability (HRV) testing. The data before measurement phases (a), during (b–e), and after (f) were measured and statistically analyzed.

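### The tests named in 2.8 use only patients with both values in any first-to-last comparison, so the arms are compared among completers; a mixed model would use every recording

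*Protocol article*

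**What the plan says.** Section 2.1 plans recruitment "with a target sample size of 30 subjects", the Abstract randomises thirty, and section 2.8 of the protocol article names paired t-tests and a "two-way ANOVA with one repeated measure to analysis the data of 30 tinnitus patients".

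The outcomes are repeated in two ways. Section 2.6 states that "HRV is measured at the first acupuncture, as well as the last acupuncture". The caption of Figure 3 adds phases within a recording: "The data before measurement phases (a), during (b–e), and after (f) were measured and statistically analyzed". Section 2.8 does not say whether session or phase is the single repeated measure. THI, in section 2.7, has two time points only: baseline, and three weeks after the first acupuncture.

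Section 2.5 sets the interval over which patients can be lost: "Treatment will be conducted over a period of 3 weeks, at a frequency of 2 sessions/week", which is six sessions. The article gives no expected loss rate.

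**The concern.** A paired t-test needs both members of each pair. A classical two-way ANOVA with one repeated factor needs every level of that factor for each patient. If the factor is session, a patient with a complete first recording and no last one adds nothing to the group-by-session test. The same holds for THI, which has no other repeated factor.

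Two things are at stake.

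- **Bias.** A complete-pair comparison is sound if missingness is unrelated to the change, given arm. That is not assured here. The Discussion describes needles manipulated until deqi in one arm, and shallow insertion with sensation and manipulation prohibited in the other. Section 2.7 foresees discomfort, bruising, nausea and faintness. Patients who do not reach the last session could therefore differ between arms.
- **Information.** HRV is the primary outcome. A first-session recording that has already been made is informative about the acute response, even if no last-session recording follows.

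**Working it through.** **Inputs from the article**

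- Recruited 30 (2.1), randomised 30 (Abstract), analysed 30 (2.8).
- Sessions: 3 weeks × 2 per week = 6 (2.5).
- HRV at two sessions (2.6), with phases (a) to (f) in each sequence (Figure 3 caption). THI at two time points (2.7).
- Significance level 0.05 (2.8).

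**Assumptions, because the article gives no figure**

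- Fraction d without the last value: 10 to 20%, equal in both arms.
- Allocation 1:1, so 15 per arm (30/6 = 5 full blocks; 2.4 does not state the ratio).
- Two-sided testing.
- Correlation r between first and last value: 0.5 to 0.7, with equal variances.

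**The plan's own figure.** There is no calculation behind 30 to reproduce. The Discussion says that the sample size could not be calculated. The recruited, randomised and analysed numbers agree.

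**Step 1: who enters which analysis**

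| Analysis | Patient with first value only |
|---|---|
| First-to-last paired t-test, HRV | excluded |
| Group-by-session ANOVA, HRV | excluded |
| Group-by-phase ANOVA within the first session | kept |
| THI change, either test | excluded |

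For example, with 3 last-session values missing out of 30, the paired t-test uses 27 patients (26 degrees of freedom) and leaves 3 first-session recordings unused. A mixed model on the same data uses all 30 patients and 60 − 3 = 57 observations. This was confirmed on a simulated data set.

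**Step 2: complete pairs and standard error**

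Pairs = 30(1 − d). SE ratio against no loss = √(30/pairs).

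- d = 10%: 27 pairs, √(30/27) = 1.054.
- d = 20%: 24 pairs, √(30/24) = 1.118.

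**Step 3: the same loss in terms of power**

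The group-by-session test is equivalent to a two-sample t-test on change. By noncentral-t power at 80%, the detectable standardised difference in change is 1.06 with 15 per arm, 1.12 at 10% loss and 1.20 at 20%. Power at 1.06 falls from 80% to 75% and 70%. These effect sizes are illustrative only.

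**Step 4: what a mixed model recovers**

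Let N be the number per arm with a first value and n the number with both. In units of the common variance, and treating r as known, the variance of the mean change per arm is:

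- complete pairs: 2(1 − r)/n
- mixed model: (1 − r²)/n + (1 − r)²/N
- no loss: 2(1 − r)/N

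With n = 0.9N and r = 0.5, the mixed-model ratio to no loss is (0.75/0.9 + 0.25)/1 = 1.083, and its square root is 1.041. With r = 0.7 it is (0.51/0.9 + 0.09)/0.6 = 1.094, and its square root is 1.046.

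| Loss | Complete pairs | Mixed model, r = 0.5 | Mixed model, r = 0.7 |
|---|---|---|---|
| 10% | +5.4% | +4.1% | +4.6% |
| 20% | +11.8% | +9.0% | +10.1% |

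Most of the loss of precision therefore comes from the missing values themselves, not from the test.

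**Step 5: how likely is it that nobody is lost?**

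If losses are independent, the chance that all 30 have both values is (1 − d)³⁰: 21% at 5%, 4% at 10% and 0.1% at 20%.

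**The case against.** The strongest reply is that 2.8 does not name the repeated factor, and the Figure 3 caption makes phase a real candidate. With phase as the factor, a patient who stops after the first session keeps the full first-session recording in that session's analysis. This stands, and it limits the HRV part of the point to first-to-last comparisons. It does not remove the point: THI has only two time points, and a classical ANOVA over phases would itself drop a patient with one unusable phase.

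Second, the mixed model saves little precision for the change. This stands too, as Step 4 shows. Nor does it cure losses that depend on values never observed. What it offers is validity when loss depends on arm and on values already recorded, and the use of every recording.

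Third, rules for missing data and the analysis population may sit in a fuller protocol or analysis plan that is not shown. Agreed: their absence is not the point. The point concerns the methods that the article does name.

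A reader might also infer more than the text supports:

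- **That exactly 30 analysed patients are promised.** The number in 2.8 is most simply read as restating the recruitment target.
- **That patients who stop are deleted outright or quietly replaced, with the block list extended beyond 30.** Nothing in the article mentions deletion or replacement. A patient who stops treatment might still be measured at the planned last visit.

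**Conclusion.** The point holds in a limited form. The methods fixed in 2.8 are complete-pair methods for any first-to-last comparison. That covers THI change with certainty, and HRV if session is the repeated factor. A patient without the last value leaves that comparison, and the arms are compared among completers.

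The size is modest and rests on an assumed loss of 10 to 20%: 24 to 27 of 30 patients enter, with a standard error 5 to 12% larger, of which a mixed model recovers only a small part. If nobody is lost, the mixed model gives the same group-by-session result as the ANOVA in balanced data, so the change costs nothing in that case. The case for it rests on the retained first-session recordings and the weaker missing-data assumption. It is worth making before the data are analysed, but it is not a fault that undermines the trial.

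**What to change.** In 2.8:

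- Name the repeated factor or factors. For HRV, both session and phase are measured, so a single repeated factor does not describe the data.
- Analyse all randomised patients with any HRV recording, in the arm assigned, with a linear mixed model. Include group, session, phase and their interactions as fixed effects, with random effects for patient and for session within patient. A single random patient effect is too simple: it ignores the correlation among phases of one session and can understate the standard error of the group-by-session contrast.
- Use the same approach for THI at its two time points. With one value per time point, the patient effect is the only random effect needed.
- Treat the paired t-tests as descriptive within-arm summaries, not as comparisons of the arms.
- Report the number of patients contributing at each session, by arm.

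The cost is a few sentences in 2.8, standard software and slightly more modelling work. The downside is that the number with a last-session value may have to be reported as below 30.
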